## Statistical analysis and data management

Analysis for baseline characteristics will be through descriptive statistics and level of significance at 0.05% will be considered significance. Results will be analysed by Intention-to-treat analysis in which clusters are analysed as to their group which were randomized prior will be used to determine the mean differences between arms using t-tests or Wilcoxon test (as appropriate) and mixed effects regression modelling of cataract surgery acceptance rate will be done so as to account for clustering at the ward level. Results will be reported as the difference in primary and secondary outcome between the intervention and control arms. We will conduct sensitivity analyses controlling for any imbalances in remaining baseline characteristic at participant and cluster level. Because mixed effects models are robust to data missing at random (MAR), we will assess data missingness. If missing data are not MAR, we will conduct multilevel multiple imputation.

Further quantitative descriptive analyses will be used to provide an understanding of the trial results that require further explanation (e.g. control clusters that demonstrate substantial improvement in outcomes, despite not receiving intervention, and reason for not attending surgery).

The trial will be reported using the 2012 CONSORT guidelines, with the updated cRCT extension [39].

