## Description of variables

### Outcomes variables

#### Primary outcome

The primary outcome will be the proportion of all eligible persons with operable cataract who accepted and show up for cataract surgery at the base hospital overall and stratified by age, sex, and VA levels. Based on the 2022 population census, the appropriate population of people aged 50 years and above will be sought from the ward authorities for denominator calculation.

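### The missing-data rule makes multilevel multiple imputation depend on a finding of 'not MAR' that observed data cannot give, and standard imputation would not correct the bias if MAR failed

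*Protocol article*

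**What the plan says.** The Protocol article, under Statistical analysis and data management, plans a model-based analysis: "mixed effects regression modelling of cataract surgery acceptance rate will be done so as to account for clustering at the ward level". On missing data it gives a two-step rule. The first step is "Because mixed effects models are robust to data missing at random (MAR), we will assess data missingness". The second is "If missing data are not MAR, we will conduct multilevel multiple imputation".

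The rule names no variable or patient group. It does not say how a failure of MAR would be established, and it does not say that the imputation would build in a departure from MAR. The only sensitivity analyses named in that section concern covariates: "We will conduct sensitivity analyses controlling for any imbalances in remaining baseline characteristic at participant and cluster level".

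The Primary outcome section ties the endpoint to attendance at the base hospital: "The primary outcome will be the proportion of all eligible persons with operable cataract who accepted and show up for cataract surgery at the base".

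**The concern.** The rule has two separate faults.

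- **The trigger cannot be evaluated.** MAR and its failure differ only in how missingness depends on values nobody has seen. Observed data can contradict missingness completely at random. They cannot show MAR to be false without assumptions that are themselves untestable.
- **The remedy does not match the trigger.** Standard multilevel multiple imputation rests on MAR, as does the mixed model it would replace or supplement. If MAR fails, both are biased.

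At stake is how results are labelled and trusted. A team that followed the rule could report an imputed estimate as the answer to non-random missingness when nothing had been corrected. This is not a detail left to the analysis plan: the article fixes a conditional rule, and a plan that carried it out faithfully would inherit the fault.

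**Working it through.** The plan states no figure here, so there is none to reproduce. The check is by reasoning, then by an illustration with assumed inputs.

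**1. Why the trigger fails.** Let Y be surgery uptake (1 or 0), X the recorded variables including arm and ward, and R = 1 if Y is recorded. Write

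odds(Y=1 | X, R=0) = exp(δ) × odds(Y=1 | X, R=1).

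MAR is δ = 0. The right-hand odds can be estimated; the left-hand odds cannot, because Y is never seen when R = 0. Every value of δ fits the recorded data equally well, so no assessment of those data can reject δ = 0.

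**2. Why the remedy fails.** A likelihood-based mixed model and standard multilevel imputation both set δ = 0. Changing from one to the other leaves δ where it was.

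**3. Simulation.** All inputs are assumed: 40 wards per arm (the planned number), 60 persons with operable cataract per ward, nominal uptake 25% and 25% × 1.30 = 32.5%, 300 replicates, 10 imputations. The imputation model used arm, ward and one covariate. In the second scenario, persons without surgery had unknown status in 40% of cases in the intervention arm and 15% in control; persons with surgery had unknown status in 5% of cases in both arms.

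| Missingness | Complete data | MAR-based multilevel imputation | Available-case ward means |
|---|---|---|---|
| MAR (depends on covariate and arm) | 0.073 | 0.073 | 0.062 |
| Not MAR (depends on the outcome) | 0.073 | 0.154 | 0.157 |

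Entries are mean risk differences, with Monte Carlo standard errors of about 0.001. Imputation recovers the complete-data value under MAR. It leaves nearly all the bias in the case for which the protocol reserves it. The comparator is unadjusted ward means, not the planned mixed model.

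**4. Hand check of the second scenario, ignoring ward and covariate variation.**

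- Control: (0.25 × 0.95) / (0.25 × 0.95 + 0.75 × 0.85) = 0.2375 / 0.875 = 0.271.
- Intervention: (0.325 × 0.95) / (0.325 × 0.95 + 0.675 × 0.60) = 0.30875 / 0.71375 = 0.433.
- Difference: 0.433 − 0.271 = 0.161 from unrounded values, against a true 0.325 − 0.25 = 0.075.

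**5. The same scenario with unknown status counted as not operated.** The rates become 0.2375 and 0.30875, the difference 0.071 and the ratio 0.30875 / 0.2375 = 1.30. Under these assumptions the distortion of the primary comparison almost disappears, so the counting convention decides how much the faulty rule matters there.

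**The case against.** The strongest defence is that the rule will seldom touch the primary outcome. Under the outcome definition, a referred person who did not go to the base hospital is an observed non-event, not a missing value. The protocol provides for finding this out: a database tracks referred persons (Data collection tools), Table 1 lists follow-up of non-attenders by study coordinators, and the analysis section plans to describe reasons for not attending surgery, which presumes that non-attendance is known. The Primary outcome section also takes a denominator from the census population aged 50 and over, and the sample size works in rates per person-year. On that reading the numerator is a count of operations per ward, with little person-level outcome to impute. This stands, and it limits the consequence.

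A reader might nevertheless infer that the rule is aimed at referred patients who did not go and that it would bias the trial's main result. The documents do not support that, because the rule names no such group. One can construct a purely hypothetical case: true uptake 25% in both arms, 20% unknown in control and 10% in intervention, and all unknowns not operated. Imputing under MAR then gives 0.25/0.80 = 31.3% and 0.25/0.90 = 27.8%, a ratio of 0.89 (1.13 with the arms reversed). Those persons are ones the definition already counts as not operated, and none of the unknown fractions comes from the protocol.

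A second defence is charitable: 'not MAR' might mean not MAR given only the variables in the mixed model, so that imputation with extra variables would make MAR more plausible. That would be sensible, but the text does not say it and names no such variables. Nor does the text claim that the mixed model copes with missing covariates, so it should not be faulted for that.

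**Conclusion.** The point holds as a fault in the stated rule. The trigger cannot be evaluated, and the named method, in its standard form, shares the assumption whose failure is meant to invoke it. This follows from the definitions and needs no figures from the trial.

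The size of any effect on the results cannot be derived from the documents. For the primary outcome it is probably small, provided referred persons with no base-hospital surgery record count as not operated. The definition implies this convention but the article does not state it in so many words. The rule matters mainly for surgery status that is truly unknown, for participant-level covariates in the adjusted sensitivity analyses, and for the acceptability and appropriateness questionnaires, where nonresponse is plausible and no outcome definition settles it. The 0.154 against 0.073 shows the mechanism under assumed missingness; it is not an expected bias here. The correction should be made because it is cheap and the rule is wrong as written, not because the main result has been shown to be at risk.

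**What to change.** Replace the two sentences on missing data with text that does four things:

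1. Delete the step of deciding whether data are MAR.
2. Confirm that a referred person with no surgery record at the base hospital counts as not operated.
3. Present the mixed model, and multilevel imputation where covariates or questionnaire items are missing, as analyses valid under MAR.
4. Prespecify a sensitivity analysis to departures from MAR for whatever remains unknown, run regardless of any test. Delta-adjusted or pattern-mixture imputation by arm is one suitable choice among several, and the range of departures can be left to the analysis plan.

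The cost is a few sentences and one small extra sensitivity analysis. Conduct, sample size and data collection do not change.

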## Coordinating centre

The research team at the University of Dodoma will provide on-site support and implementation of the study.

## Monitoring

Institutions offering ethical clearance and local government authorities will be monitoring the study closely. There will also be an advisory committee composed of local expert and specialists in this field. Data will be collected through use of portable electronic devises, which will be securely backed up and cleaned on daily basis. We do not plan to perform an interim data analysis of the primary outcome. But maybe we will do an interim safety analysis after the first year of the cRTC looking at rates of adverse surgical outcomes with a plan to pause the trial and evaluate the causes if these rates are substantially higher than the current average in Tanzania.

## Participant and public involvement statement

This community-led intervention trial offers a maximum involvement of the community and participants. Community perceptions of the intervention will be determined from time to time and if anything is not working well then mitigation measures will be set in place to make sure the study is implemented as expected by the community. Results of the intervention implementation process will be shared through quarterly wards meetings, which all community members will be invited to attend, and where they will be able to make recommendations for refinement of the intervention package.

## Ethics and dissemination

The study protocol has received ethical clearance from National Institute for Medical Research of Tanzania and the University of Cape Town.

We aim to publish the initial qualitative data on co-creation process and end project progress papers in peer-reviewed scientific articles in open access journals.

## Discussion

This community-led trial is intended to develop and implement a ‘community-led intervention package’ for increasing cataract surgery uptake in rural Tanzania.

Dodoma is one of the regions in Tanzania with a high prevalence of cataract blindness. It has also been among the hardest hit by trachoma due to water scarcity. It is believed that the intervention package developed by the community might address these additional ocular conditions by improving presentation to community eye health outreach camps.

The IAPB and WHO target to eliminate avoidable blindness has come to an end and been updated to the concept of integrated people-centred eye care, which this study is built upon [40]. This study is novel in using a community-led participatory action research approach for development of the intervention and a cluster-randomized trial methodology for rigorously assessing if the package of community-led intervention(s) will bring about the desired changes. If the results of the trial are positive, a plan for scaling up to other rural areas will be devised.

## Data Availability

There are no data collected for now, but the randomization process can be made available if requested. Data will be made available at Open Science Framework (OSF- osf.io/48jmq) research management and collaboration tool.
